### Length of stay

Admission time is measured and expressed in two ways: from arrival time at the A&E department until discharge and from end of surgery to until discharge. The discharge criteria in all participating centers are: NRS-pain score below 5 without need for parenteral analgesics and an Elderly Mobility Scale (EMS) score 14 out of 20 or higher [63, 64]. If this some items were deemed unobtainable EMS scores are completed until transfer to a nursing home is arranged. If family members are able to foresee in certain home care aspects the patient can be discharged to his/her home. The fulfillment of this care by family is noted and corrected for afterwards.

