### Aim

The aim of the current study is to evaluate the efficacy of CFC therapy on pain in the first 72 postoperative hours of hip fracture patients. The secondary aim is to evaluate the effects on (non-) morphine analgesic use; postoperative hemoglobin level; transfusion incidence; delirium incidence and severity; use of psychotropic medication; length of stay; short-term location and duration of rehabilitation; functional outcome; short-term patient-reported health outcome; general and cryotherapy related complications. Furthermore the feasibility of a cryocompression device on orthopedic/surgery wards is assessed.

We hypothesized that: 1) CFC therapy will lower perceived pain levels and morphine consumption; and 2) will reduce postoperative blood loss and transfusion incidence; and 3) reduced pain by CFC therapy will lead to lower delirium incidence and 4) enhance functional recovery, leading to shorter length of stay in postoperative hip facture patients.

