### Randomization

A balanced 1:1 block (size six) randomization stratified by center will be performed directly after surgery, using Research Manager (RM; version 4.5.0.1), a web-based computer program (Fig. 1). A research nurse who is not involved in the study generates the allocation sequence with RM. Intramedullary hip nail (IMHN), dynamic hip screw (DHS) and cannulated screws are grouped for block randomization, as are total hip arthroplasty (THA) and hemiarthroplasty (HA). The intervention group ‘A’ will receive CFC therapy postoperative; the control group ‘B’ will receive standard care. Due to the nature of the study no blinding can exist as patients, family and physicians notice the use and settings of CFC therapy. Physicians randomize participants with a digital logon to the web-based system or the physician can contact the coordinating investigator and he will randomize the included participant (see Table 1 for criteria).The Informant Questionnaire for the Cognitive Decline in the Elderly (IQ-CODE) questionnaire is administered when the clinician has doubts about the cognitive state that may compromise CFC therapy sessions or study measurements (Table 1). Ideally a MMSE would be used for this purpose, however due frequently perceived pain at the accident and emergency A&E department and consequently administered narcotic analgesics, the hetero anamnestic IQ-CODE is used instead. The coordinating investigator contacts the participating hospitals on a daily basis by telephone or physically to ensure adequate and appropriate enrollment of participants and completeness of data. A list of excluded patients will be drafted.

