## Statistics

### Analysis of outcome parameters

All statistical analyses will be computed using the SPSS statistical package (IMB SPSS, Inc., Release 20.0.0.0, 64-bit edition). Statistical analysis will be performed according to the intention-to-treat principle. Baseline characteristics will be described in accordance with CONSORT guidelines [41] using means and standard deviation in case of normal distribution, and medians and interquartile ranges otherwise. Continuous variables will be checked for normality, visually and by using the Shapiro Wilk test. Our primary analysis focuses on the differences in NRS-pain scores between the study groups 24 h postoperative and will be analyzed by use of Student’s T or Mann–Whitney U tests in case of skewed distribution. To assess treatment effect over time, a mixed model analysis for repeated measures will be performed. This model allows missing data and adjustment for serious confounders and interactions. In case of skewed distributions and outliers non-parametric variants will be used (e.g. Mann Whitney U or Friedman tests). Secondary continuous outcome measures (EQ-5D-3L, SF-12, DRS-R-98 and hemoglobin) will be compared by use of Student’s t or Mann Whitney U tests. Ordinal variables will be analyzed using the Mann–Whitney test. Chi-squared tests will be performed in case of categorical variables. In case of important confounding, analysis will be adjusted to correct for these factors (by use of multiple regression analysis, linear or logistic). A *p*-value of < 0.05 will be considered statistically significant.

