Currently three of the four participating hospitals have a geriatric trauma unit, in one of the hospitals with a geriatric trauma unit the care of the surgical geriatric patient is transmitted to the geriatrician in full except for wound assessments and related care. At this ward all patients receive prophylactic haloperidol 1 mg daily, and more if needed. At the hospital without a geriatric trauma unit a geriatrician is not readily available and unable to attend the clinic on a daily basis. Confounding of secondary outcomes as delirium, psychotropic medication and functional outcome can therefore not be ruled out.

When compared to the preoperative values, hemoglobin levels in collected blood samples at postoperative day one are usually much lower than one would expect from the observed blood loss during surgery. This gap called ‘the hidden blood loss’ is thought to arise from, among others gastro-intestinal bleeding [22, 79]. The amount of (hidden) blood loss is more severe when oral anticoagulants or thrombocyte aggregation inhibitors compromise a patient’s hemostasis and this loss may continue throughout the early postoperative period. Hemoglobin measured at postoperative day one is most likely, as opposed to the preoperative values, significantly diluted, thereby underestimating the actual hemoglobin concentration. Combined with the possibility of hidden blood loss throughout the hospital stay, care has to be taken when comparing the value of postoperative day one to day three.

The functional outcome assessment of patients who are not allowed to bear weight at the time of discharge is postponed to the outpatient clinic. At this visit they are allowed to bear weight for the first time in weeks. Testing directly after weight bearing for the first time can introduce confounding.

Finally, care has to be taken to interpret the allocation to rehabilitation facilities. For instance patients who have sufficient family members who can help out at home are more likely to be discharged home with or without homecare rather than be assigned to a rehabilitation clinic or nursing home with rehabilitation facilities.

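### Correcting length of stay for fulfilled family care adjusts for a post-randomisation variable and can distort the treatment effect on this secondary outcome

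*Protocol article*

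**What the plan says.** The Length of stay section of the protocol article sets discharge criteria on pain and mobility: "NRS-pain score below 5 without need for parenteral analgesics and an Elderly Mobility Scale (EMS) score 14 out of 20 or higher". It then describes a route through relatives: "If family members are able to foresee in certain home care aspects the patient can be discharged to his/her home". The next sentence is the analysis rule at issue: "The fulfillment of this care by family is noted and corrected for afterwards". It carries no condition. The general rule in Analysis of outcome parameters does carry one: "In case of important confounding, analysis will be adjusted to correct for these factors".

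Three other places bear on it:

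- **Timing** (Randomization): "A balanced 1:1 block (size six) randomization stratified by center will be performed directly after surgery".
- **Hypothesis** (Aim): treatment is expected to "enhance functional recovery, leading to shorter length of stay in postoperative hip facture patients".
- **Blinding** (Randomization): "Due to the nature of the study no blinding can exist as patients, family and physicians notice the use and settings".

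The Discussion, writing about allocation to rehabilitation facilities, adds that "patients who have sufficient family members who can help out at home are more likely to be discharged home".

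**The concern.** The covariate named is the fulfilment of care, not the existence of relatives who could give it. Fulfilment is realised after randomisation, close to the event that ends the outcome. Treatment could reach it in two ways. One is through recovery: discharge depends on pain and mobility, both of which the trial hopes to improve, and these may decide whether help at home is needed or sufficient. The other is through knowledge of allocation, which relatives and staff have and which could change willingness or discharge planning.

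If either route operates, holding fulfilled care constant removes part of what treatment does. It can also create a spurious link between arm and unmeasured recovery. The estimate then answers a different question from whether treatment shortens stay, which is one of the trial's named hypotheses. Nor is the correction needed against confounding, because randomisation already balances pre-existing family support in expectation.

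**Working it through.** **The plan's own figure.** The article gives no number for length of stay. Its only design figure is the total of 160, based on NRS-pain at 24 h (SD 2.2, difference 1.3, alpha 5 % taken as two-sided, power 90 %, dropout 22.3 %). The normal approximation gives 61 per arm and 122/(1 − 0.223) = 157.01, rounded up to 158. The t-test version gives 62 per arm and 124/0.777 = 159.6, rounded up to 160. The figure reproduces, and this point does not touch it.

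**Order of events from the text.** Surgery, randomisation, treatment, recovery to the pain and mobility criteria, family care arranged or not, discharge. Fulfilled care therefore falls after allocation. Having relatives falls before it.

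**Illustration.** Every input here is an assumption. Let A be the arm (1:1), V family availability before randomisation, R recovery, F fulfilled family care and L length of stay in days. U, V and e are independent standard normal.

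- R = τA + U
- logit P(F = 1) = −0.4 + 1.0·V + a_R·R + a_A·A
- L = 8 − 1.0·R − 1.0·F + 1.5·e

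So 1 SD of recovery and fulfilled care each shorten the stay by 1 day. With 2,000,000 simulated patients per scenario, L was regressed on A, on A and F, and on A and V.

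| Scenario | τ | a_R | a_A | F = 1, control / treated | Effect on L, not corrected (d) | Corrected for F (d) | Shift |
|---|---|---|---|---|---|---|---|
| F fixed by availability alone (V > 0.3) | 0.4 | – | – | 0.382 / 0.383 | −0.404 | −0.403 | nil |
| F unrelated to arm and recovery | 0.4 | 0 | 0 | 0.417 / 0.419 | −0.402 | −0.401 | nil |
| F likelier with better recovery | 0.4 | 0.5 | 0 | 0.420 / 0.459 | −0.437 | −0.382 | 13 % toward zero |
| Same, stronger | 0.4 | 1.0 | 0 | 0.428 / 0.500 | −0.473 | −0.349 | 26 % toward zero |
| F less likely with better recovery | 0.4 | −0.5 | 0 | 0.421 / 0.382 | −0.365 | −0.388 | 6 % away from zero |
| Same, stronger | 0.4 | −1.0 | 0 | 0.429 / 0.358 | −0.329 | −0.348 | 6 % away from zero |
| No effect on recovery or care | 0 | 1.0 | 0 | 0.427 / 0.427 | 0.001 | 0.002 | nil |
| Allocation itself shifts F | 0 | 1.0 | 0.5 | 0.428 / 0.519 | −0.092 | +0.065 | sign reverses |

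**Check by hand.** The total effect is −1.0·τ − 1.0·(difference in F). For a_R = 1.0 this is −0.4 − (0.500 − 0.428) = −0.472, against −0.473 simulated. For a_R = −1.0 it is −0.4 + (0.429 − 0.358) = −0.329, as simulated. In the last row it is −(0.519 − 0.428) = −0.091, against −0.092.

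**What the corrected column estimates.** In rows 3 to 6 the part of the effect that bypasses family care is −0.40, and in the last row it is 0. The corrected estimates (−0.382, −0.349, −0.388, −0.348, +0.065) match neither that nor the total, because F also carries information on unmeasured recovery. The reversal in the last row needs both links. If care responded to allocation but not to recovery, the corrected effect would be zero, since nothing else in that model ties arm to stay.

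**Adjusting for V instead** gave −0.403, −0.402, −0.437, −0.474, −0.365, −0.329, 0.001 and −0.092, within 0.001 d of the uncorrected effect in every row.

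**A second set of assumptions.** 1,500 trials of 160 patients, half with family available, care shortening stay by 2 days. Care used once function allows home discharge: −0.71 d total against −0.53 d corrected (0.18/0.71 = 25 % toward zero). Care used only when function is poor: −0.44 d against −0.49 d (0.05/0.44 = 11 % from these rounded values, 12 % unrounded, away from zero). The remaining inputs of that run are not available to show here, so it supports the pattern only.

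**The case against.** The strongest reply is that family care is mainly a social circumstance that exists before randomisation. The Length of stay section ties it to whether relatives are able to help, and the Discussion to having enough of them. Neither mentions recovery, and the Discussion sentence concerns rehabilitation placement, not length of stay. A reader might infer that fulfilled care depends on recovery and that the correction therefore does bias the result. The documents do not support that: the dependence is a plausible inference from the discharge criteria and the Aim, not a statement. If it is absent and allocation has no direct influence, the bias is nil, as the table shows.

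Second, a reader might infer that the corrected estimate replaces the intention-to-treat comparison. The article does not say so. It names intention-to-treat as the governing principle, and correcting afterwards could mean a supplementary analysis.

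Third, the shifts are small beside sampling error. With 80 per arm the standard error is SD·√(2/80) = 0.158·SD. For an assumed SD of 3 to 6 d that is 0.47 to 0.95 d, so even a shift of 0.18 d is under 0.4 of a standard error.

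All three limit the claim. None supplies a reason for the rule. The variable named is fulfilment, the commitment is unconditional, and the rule is harmless only if treatment leaves family care untouched, which sits uneasily with the trial's own hypothesis and its open-label design.

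**Conclusion.** The point holds in limited form. The article commits to correcting length of stay for something realised after randomisation, around discharge. Should treatment influence it through recovery or known allocation, the corrected figure is not the total effect of treatment on length of stay.

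Direction and size cannot be fixed from the documents. Under the assumed inputs the shift lay between 0 % and about 26 % toward zero, or about 6 to 12 % away from zero, with a possible change of sign if allocation itself alters family care. These percentages illustrate the mechanism and do not predict the trial's result. One secondary outcome is concerned; the NRS-pain analysis and the 160 patients are unaffected.

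**What to change.** Replace the correction sentence with three statements:

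1. The main analysis of length of stay is the intention-to-treat comparison between arms, not corrected for fulfilled family care.
2. If adjustment for family support is wanted, the covariate is availability of family help (yes/no) recorded at admission, before randomisation.
3. Fulfilled family care and discharge destination are reported descriptively by arm.

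The cost is a short change of analysis wording and, only if the adjusted analysis is kept, one yes/no admission item. Table 4 does not itemise demographics, so that item may already be collected. Sample size, visits and the primary analysis do not change.

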### Functional outcome

#### Timed Up and Go Test

The TUGT is a functional mobility test that measures the time it takes a patient to get up out of a chair, walk 3 m and return in a sitting position. The test is easy to use and has sufficient clinometric characteristics [65], can predict short-term risk of new falls [66] and functional outcome over time [67]. Detailed instructions are provided to the patient: rise from the chair (knees at 90° flexion) when you hear “go”, walk at safe speed to the mark on the floor and back, the time stops when you hit the chair with your buttocks. The physical therapist will demonstrate how to perform the TUGT once. The average of three tests will be the final TUGT outcome and no trial run is performed. Postoperative mobilization policy is noted and patients are stratified in three groups: no weight bearing, partial weight bearing or full weight bearing. Preferably no walking aid will be used during the test but if needed, the patient can use any walking aid available, the type of aid used will be recorded. The updated NMS is administered at inclusion for data stratification purposes [44, 45, 68]. NMS will be classified as low when NMS is 2-6 and scored high when NMS is 7–9 [46].

#### De Morton Mobility Index

The DEMMI is a measure of mobility that has been validated in hip fracture patients [69-71]. The DEMMI is administered by physician or physical therapist observation of the test subject’ physical performance, measured in 15 hierarchical domains (three bed, three chair, four static balance, two walking and three dynamic balance items), each measured on a two (able/unable) or three (able/partial/unable) point scale. It takes a trained person ten minutes to administer the test in elderly patients. The raw score is converted to an interval score.

#### Short Physical Performance Battery

The SPPB is composed of three tasks: a hierarchical balance task, a short walk at normal speed, and five repetitive chair stands. Low scores in the SPPB have predictive value for a wide range of health outcomes: mobility loss, disability, hospitalization, length of hospital stay, nursing home admission, and death [72-75]. Normative values of SPPB have been published for representative populations by five-year age groups and sex [73]. The strong and consistent association with health status measures demonstrated the validity of the SPPB [76].

### Patient reported outcome measures

#### EQ-5D-3L

The EuroQol/EQ-5D-3L is a validated, generalized and standardized instrument comprising a VAS measuring self-rated health and a health status instrument, consisting of a three-level response (no problems, some problems and extreme problems) for five domains related to daily activities; (i) mobility, (ii) self- care, (iii) usual activities, (iv) pain and discomfort and (v) anxiety and depression. Responses to the health status classification system are converted into an overall score using a published utility algorithm for the Dutch population [77]. A respondent’s EQ-VAS gives self-rated health on a scale where the endpoints are labeled ‘best imaginable health state’ (100) and ‘worst imaginable health state’ (0).

#### Short Form-12

The SF-12 is the abbreviated version of the original SF-36 and scores quality of life in two domains, physical and mental health. It has shown good correlation with the SF-36 and proved valid in many conditions, amongst is orthopedic surgery [78].

### Complications

The surgeon monitors all complications that may occur throughout admission, in general or cryotherapy-related. After discharge the coordinating investigator verifies if all adverse events are registered and recorded on the appropriate CRF. In case of serious adverse events relating to the treatment patients will no longer receive treatment but will remain in the study for follow-up, if feasible. Severe leakage i.e. multiple bandage swaps daily is noted and registered as an adverse event. Furthermore an intragroup analysis of vital signs is made to determine possible central effects of the administered therapy. Finally, at the outpatient visit patients are assessed for adverse events that may have occurred during rehabilitation. Additional to the patient questionnaire (Table 5), intervention patients are asked about their experiences with CFC therapy. An additional insurance is taken out to financially compensate participants if applicable. Adverse events are tabulated and reported in the final manuscript.

### Feasibility

At the end of the study nursing staff will complete questionnaires specifically drafted for this study (Table 6) and the booklet of prevalent technical problems will be evaluated. A close out visit will be planned in which recommendations for further improvement of the machine will be discussed. Treatment failure i.e. discontinuation of treatment is reported and provided with reasons e.g. discomfort.

**Table 6 Tab6:** Nursing staff questionnaire

1. Was the GRS hip/groin wrap technically easy to apply?	A	B	C	D	E
2. Was the GRS hip/groin wrap easy to apply to postoperative hip fracture patients?	A	B	C	D	E
3. Did you apply the GRS hip/groin wrap alone?	Y				N
4. Was the control unit easy to operate?	A	B	C	D	E
5. If the GRS works do you think that the application (4 times 30 min a day) is feasible in daily practice?	A	B	C	D	E
6. Were you able to administer all the treatments that were required?	A	B	C	D	E
7. Would you recommend cryocompression therapy to patients?	A	B	C	D	E
8. Do you think patients recovered faster because of cryocompression therapy?	A	B	C	D	E
9. Should the cryocompression therapy be apart of standard hip fracture treatment?	A	B	C	D	E
10. Can you briefly describe what you think are advantages of cryocompression therapy?	Open text				
11. Can you briefly describe what you think are disadvantages of cryocompression therapy?	Open text				

*GRS* Game Ready system

A: agree completely; B: agree; C: neutral; D: disagree; E: disagree completely

Y: yes; N: no

## Statistics

### Analysis of outcome parameters

All statistical analyses will be computed using the SPSS statistical package (IMB SPSS, Inc., Release 20.0.0.0, 64-bit edition). Statistical analysis will be performed according to the intention-to-treat principle. Baseline characteristics will be described in accordance with CONSORT guidelines [41] using means and standard deviation in case of normal distribution, and medians and interquartile ranges otherwise. Continuous variables will be checked for normality, visually and by using the Shapiro Wilk test. Our primary analysis focuses on the differences in NRS-pain scores between the study groups 24 h postoperative and will be analyzed by use of Student’s T or Mann–Whitney U tests in case of skewed distribution. To assess treatment effect over time, a mixed model analysis for repeated measures will be performed. This model allows missing data and adjustment for serious confounders and interactions. In case of skewed distributions and outliers non-parametric variants will be used (e.g. Mann Whitney U or Friedman tests). Secondary continuous outcome measures (EQ-5D-3L, SF-12, DRS-R-98 and hemoglobin) will be compared by use of Student’s t or Mann Whitney U tests. Ordinal variables will be analyzed using the Mann–Whitney test. Chi-squared tests will be performed in case of categorical variables. In case of important confounding, analysis will be adjusted to correct for these factors (by use of multiple regression analysis, linear or logistic). A *p*-value of < 0.05 will be considered statistically significant.

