**Methods/design:**

One hundred and sixty patients with an intra or extracapsular hip fracture scheduled for internal fixation (intramedullary hip nail, dynamic hip screw or cannulated screws) or prosthesis surgery (total hip or hemiarthroplasty) will be included in this prospective, open-label, parallel, multicenter, randomized controlled, clinical superiority trial. Patients will be allocated to two treatment arms: group ‘A’ will be treated with continuous-flow cryocompression therapy and compared to group ‘B’ that will receive standard care. Routine use of drains and/or compressive bandages is allowed in both groups. The primary objective of this study is to compare acute pain the first 72 h postoperative, measured with numeric rating scale for pain. Secondary objectives are: (non-) morphine analgesic use; adjusted postoperative hemoglobin level; transfusion incidence; incidence, duration and severity of delirium and use of psychotropic medication; length of stay; location and duration of rehabilitation; functional outcome; short-term patient-reported health outcome; general and cryotherapy related complications and feasibility.

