## Outcome parameters

### NRS-pain (primary)

The verbally administered 11-point (range 0–10) NRS-pain is a widely accepted assessment tool and has been validated in many different conditions, among is acute pain in the emergency department [53–55]. Reliability and validity has been thoroughly studied in (cognitively impaired) elderly and has shown to maintain acceptable clinometric characteristics [56–58]. NRS-pain scores are compared within the intervention group i.e. pre and post-treatment and compared between the intervention and control groups. Cumulated pain scores will be calculated for both groups by adding the (post-treatment) pain scores of the first 72 postoperative hours.

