### Sample size calculation

Sample size calculation is based on the primary outcome measure, NRS-pain at 24 h postoperatively. Subsequently, a mean NRS-pain score for postoperative day one was drawn from the Spaarne Gasthuis electronic patient dossier digital databanks and a standard deviation of 2.2 was calculated for pooled internal fixation and (hemi) arthroplasty for cervical and peritrochanteric fractures. The minimal clinical relevant difference for NRS-pain is 1.3 out of 10 [53]. The alpha was set at 5 % with a power of 90 % due to anticipated heterogeneity in regard to operating techniques, general care protocols but predominantly in regard to pain protocols between the participating centers (Table 2). An expected NRS failure rate of 10 % is anticipated together with expected missing data a drop out of 22.3 % is computed. The total number of included patients will be 160.

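### The stated primary objective is pain over the first 72 hours, but the primary analysis and the sample size rest on a single score at 24 hours

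*Protocol article*

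**What the plan says.** The protocol article describes the primary question in five places.

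- **Abstract, Methods/design:** "The primary objective of this study is to compare acute pain the first 72 h postoperative, measured with numeric rating scale for pain".
- **Background, Aim:** the purpose is to "evaluate the efficacy of CFC therapy on pain in the first 72 postoperative hours of hip fracture patients".
- **Outcome parameters, NRS-pain (primary):** this section lists comparisons within the intervention group and between groups, then adds: "Cumulated pain scores will be calculated for both groups by adding the (post-treatment) pain scores of the first 72 postoperative hours". It names no 24-hour time point.
- **Statistics, Analysis of outcome parameters:** "Our primary analysis focuses on the differences in NRS-pain scores between the study groups 24 h postoperative", tested with Student's t or Mann–Whitney. A separate sentence adds: "To assess treatment effect over time, a mixed model analysis for repeated measures will be performed". The mixed model is not called primary.
- **Statistics, Sample size calculation:** "Sample size calculation is based on the primary outcome measure, NRS-pain at 24 h postoperatively".

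Table 3 sets cycles 1–4 at low pressure, 5–8 at medium and 9–12 at high. The fixed treatment moments are 8:00, 12:00, 16:30 and 21:30.

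**The concern.** The first three places point to a 72-hour endpoint and the last two to a 24-hour endpoint. A later analysis plan cannot be faithful to both. The difference also matters in substance, because treatment runs through the whole 72-hour window and most of it comes after the 24-hour score.

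Two misreadings follow. A positive 24-hour result could be reported as meeting a 72-hour objective that it did not test. A null 24-hour result could be taken as failure of a treatment of which at most a third of the cycles had been given. With the primary question worded two ways, a reader of the final report also could not tell which result the trial had committed itself to.

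**Working it through.** **1. The plan's own sample size.** Inputs from Sample size calculation: difference 1.3, SD 2.2, alpha 5% (taken as two-sided), power 90%, dropout 22.3%. Allocation is 1:1 (Randomization).

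- Normal approximation: n per arm = 2 × (1.960 + 1.282)² × 2.2² / 1.3² = 60.2, so 61. Total 122; 122 / (1 − 0.223) = 157.01, so 158.
- Exact t-test: 62 per arm. Total 124; 124 / 0.777 = 159.6, so 160.

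The stated 160 reproduces for the 24-hour endpoint.

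**2. Cycles completed by 24 hours under Table 3.** A 30-minute cycle counts if it ends no later than 24 hours after the end of surgery.

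| Schedule | Surgery ends | Cycles completed by 24 h | Number |
|---|---|---|---|
| A (starts 16:30) | 10:00 | 16:30, 21:30, 8:00 | 3 |
| A | 16:00 | 16:30, 21:30, 8:00, 12:00 | 4 |
| B (starts 21:30) | 16:30 | 21:30, 8:00, 12:00 | 3 |
| B | 21:00 | 21:30, 8:00, 12:00, 16:30 | 4 |
| C (starts 8:00) | 21:30 | 8:00, 12:00, 16:30 | 3 |
| C | 23:30 | 8:00, 12:00, 16:30, 21:30 | 4 |

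Running the rule over all surgery end times from 10:00 gives only 3 or 4. The earliest fifth cycle, the first at medium pressure, starts 24.5 hours after surgery in A and B and 25 hours in C. So by 24 hours 3/12 to 4/12 (25–33%) of the Table 3 cycles are done, all at low pressure, and 8 or 9 remain.

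**3. Sensitivity of that count.** The section on cryocompression therapy and clinical measurements says treatment begins 6 hours after surgery, whereas Table 3 allows a start about half an hour after surgery. With the first fixed moment at least 6 hours after surgery, the count is 2 to 4, still all at low pressure. The treatment schedule text gives 10 to 12 cycles where Table 3 shows 12. Neither discrepancy changes the direction.

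**4. What a 72-hour mean would need (illustrative).** The article gives no within-patient correlation. Assume 2.2 is a per-score SD, 12 scores and a common correlation ρ. Then the SD of the mean = 2.2 × √((1 + 11ρ)/12), and power ≈ Φ(effect / (SD × √(2/62)) − 1.96) with 62 evaluable per arm.

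| ρ | SD of mean | Power, effect 1.3 | Power, effect 1.0 |
|---|---|---|---|
| 0.3 | 1.32 | >99% | 99% |
| 0.5 | 1.62 | 99% | 93% |
| 0.7 | 1.87 | 97% | 84% |

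At ρ = 0.7 and an average effect of 0.8, power is 66%.

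**5. Power of the 24-hour test at smaller effects (assumed).** With SD 2.2 and 62 per arm: 91% at 1.3 points, 72% at 1.0 and 38% at 0.65.

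**The case against.** The strongest reply is that the plan does designate one primary. Only the 24-hour comparison carries that label in the Statistics section, a test is named for it, and the trial is sized on it. The mixed model has its own stated purpose, and no test is attached to the cumulated score. Measuring pain one day after surgery is a legitimate design choice, and the ranking of supporting analyses is commonly left to an analysis plan.

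Most of this stands, and it rules out several stronger readings that a reader might infer.

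- **Three competing primaries with an inflated error rate.** Three tests at 5% each, with assumed correlations of 0.5–0.8, would give a 10–13% chance of at least one false positive; two tests would give 8–9%. These figures are illustrative only: the article labels one analysis primary and gives no correlations.
- **A 24-hour score that tests a barely delivered treatment.** The article plans the coldest setting from the first cycle, if feasible; only pressure is stepped up. Nothing in it says that pain relief depends on pressure or builds over cycles.
- **A sample size of 160 that simply carries over to a 72-hour mean.** The SD was obtained alongside a mean score for postoperative day one and may not be a per-score SD. The correlation is unknown, and a constant 1.3-point effect is assumed.

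The reply does not remove the contradiction. If the Statistics section prevails, the Abstract and Aim misstate the primary objective and the primary outcome section never names the primary time point.

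**Conclusion.** The point holds as an internal contradiction that limits what the trial may conclude. The objective and outcome text describe 72 hours; the confirmatory test and sample size describe 24 hours. By then 3 or 4 of up to 12 cycles are complete under Table 3 (2 to 4 under the 6-hour start), all at low pressure, so the test cannot by itself establish efficacy over 72 hours.

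The count assumes that cycles follow the fixed clock times and that the score is taken at 24 hours. If it were taken after the nearest fixed session, a few patients could already have had a fifth cycle. The contradiction itself depends on none of these assumptions. The sample size calculation is not at fault, and the documents do not make a 72-hour mean the only correct primary endpoint.

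**What to change.** Name one primary endpoint and time frame, and align the Abstract, the Aim, NRS-pain (primary), Analysis of outcome parameters and Sample size calculation to it, by amendment before the data are analysed. Either option resolves the contradiction.

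- **(a) Keep 24 hours.** The sample size of 160 stands as calculated. Reword the objective and Aim, limit the primary claim to pain at 24 hours, name that time point in the outcome section, and label the mixed-model and cumulated 72-hour results secondary.
- **(b) Move to 72 hours.** Make the between-arm difference in mean NRS over 72 hours, from the mixed model already planned, the primary analysis, with the 24-hour contrast as first secondary. Rewrite the sample size paragraph for that endpoint, stating whether 2.2 is a per-score SD, the assumed within-patient correlation and the average effect. Do not carry 160 over without that calculation.

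Separately, reconcile the 6-hour start with the Table 3 start times, and the 10-to-12 cycle count with the 12 in Table 3, so that treatment received before the primary time point is defined.

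Option (a) costs wording only. Option (b) adds a short recalculation. Neither needs new measurements, since pain scores are already planned through 72 hours. Whether (b) needs more patients depends on the recalculation: under the assumptions above it does not at 1.3 points, but power falls short of 90% at an average effect of 1.0 with correlation 0.7.
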